# A cluster randomized controlled trial of a behavioral intervention to facilitate the development and implementation of clinical practice guidelines in Latin American maternity hospitals: the Guidelines Trial: Study protocol [ISRCTN82417627]

**DOI:** 10.1186/1472-6874-5-4

**Published:** 2005-04-11

## Abstract

**Background:**

A significant proportion of the health care administered to women in Latin American maternity hospitals during labor and delivery has been demonstrated to be ineffective or harmful, whereas effective interventions remain underutilized. The routine use of episiotomies and the failure to use active management of the third stage of labor are good examples.

**Methods/Design:**

The aim of this trial is to evaluate the effect of a multifaceted behavioral intervention on the use of two evidence-based birth practices, the selective use of episiotomies and active management of the third stage of labor (injection of 10 International Units of oxytocin). The intervention is based on behavioral and organizational change theories and was based on formative research. Twenty-four hospitals in three urban districts of Argentina and Uruguay will be randomized. Opinion leaders in the 12 intervention hospitals will be identified and trained to develop and implement evidence-based guidelines. They will then disseminate the guidelines using a multifaceted approach including academic detailing, reminders, and feedback on utilization rates. The 12 hospitals in the control group will continue with their standard in-service training activities. The main outcomes to be assessed are the rates of episiotomy and oxytocin use during the third stage of labor. Secondary outcomes will be perineal sutures, postpartum hemorrhages, and birth attendants' opinions.

## Background

In Latin American maternity hospitals, a significant proportion of the health care administered to women during labor and delivery has been demonstrated to be ineffective or harmful, whereas proven effective interventions are underutilized. For example, routine episiotomy use has been documented to be useless and even harmful [1], yet the episiotomy rate in vaginal births of primiparous women in Latin American hospitals is 92 %. [2]. The caesarean section rate in Latin American countries is above 25% for the region as a whole, resulting in approximately 850,000 unnecessary cesarean sections performed each year [3]. Simultaneously, many of the birth practices verified as beneficial are not routinely used, e.g. active management of the third stage of labor has been proven effective to prevent postpartum hemorrhage, one of the leading causes of maternal deaths in the developing world [4]. In a survey in 19 maternity services of Uruguay and Argentina, 17 (89.5%) used expectant management as the standard form of care (unpublished observation). Another practice that has been proven to be beneficial and without adverse effects is a companion accompanying women in labor and delivery [5]; however, only 21% of women had a companion in the survey of the 19 hospitals mentioned above. The administration of enemas at admission in labor, perineal shaving, and systematic intravenous infusion are other examples of practices not supported by scientific evidence which are still in widespread use in Latin American hospitals [6,7].

### Barriers to the adoption of evidence based birth practices

Why, despite scientific evidence and active dissemination of scientific information, are harmful or unnecessary procedures (or both) still used, whereas other beneficial procedures are ignored?

It is postulated that a wide variety of barriers can hinder practitioners from adhering to evidence-based practices, thus a theoretical framework may help delineate these barriers and possibly help target specific interventions to address appropriate practice patterns. Cabana et al. published a comprehensive systematic review about the barriers to physician adherence to practice guidelines and developed a theoretical approach to the barriers [8].

They reviewed 76 articles including five qualitative studies and data from 120 surveys to identify possible barriers to guideline adherence. Barriers were classified into seven general categories: barriers affecting physician knowledge (lack of awareness and lack of familiarity); those affecting attitudes (lack of agreement, lack of self-efficacy, lack of outcome expectancy and the inertia of previous practices); and those affecting behavior (external barriers).

One study included in Cabana's review was a survey of 38 childbirth-related organizations regarding the use of Effective Care in Pregnancy and Childbirth[9]. The survey asked what the organizations considered the main barriers to effective transfer of research information.. Every organization specifically cited the practitioners' failure to keep up with the literature, a lack of resources, and the low value placed on research evidence as major obstructions in the implementation of research findings.

Making research information accessible and comprehensible to practitioners is an important mechanism to increasing awareness and familiarity with best clinical practices; however, it is rarely independently sufficient to overcome other categories of barriers and to effectively change practice patterns [10].

### Interventions to change professional practice

Many methods designed to change medical behavior have been developed and used in industrialized countries. Several systematic reviews on that subject concluded that there are no "magic bullets" to change professional behavior and that the best approach is to combine several strategies, such as the use of local opinion leaders, convening workshops, providing outreach visits (academic detailing), and reminders, as well as the use of audits and a provision for feedback. [11,12]. A more recent review did not support this conclusion providing evidence that some single interventions might be as effective as the combined strategies, but also acknowledging that there is a need for further and improved research regarding such interventions thus providing a strong rationale and theoretical basis for the selection of their components [13,14].

Among the trials considered in the above reviews were strategies directed at behavior change of birth attendants in North America and Europe, including distribution of educational materials, employing local opinion leaders, and the use of audits and feedback directed at increasing the number of vaginal births after cesarean section [15]; nurse opinion leaders to reduce rates of epidural analgesia by increasing the amount of support to women in labor [16]; educational outreach visits to introduce Cochrane Reviews to facilitate evidence-based use of specific birth practices [17]; employing local opinion leaders, grand round lectures, chart reminders, group interactive discussions, and audits to increase the use of corticosteroids for enhancing fetal lung maturation prior to a preterm birth [18].

Very few trials of a similar nature have been performed in developing countries, and among these results were inconclusive [19,20]. To our knowledge, no randomized controlled trial has been performed to evaluate the effectiveness of an intervention to implement evidence-based birth practices in Latin American countries.

Our hypothesis is that a multifaceted intervention designed to increase birth attendant concern about the effectiveness of routinely used birth practices, to provide them with resources and skills to access, interpret, and develop evidence-based clinical guidelines, and to establish mechanisms facilitated through key hospital leaders, to implement the guidelines and sustain them over time, will increase the use of evidence-based birth practices in Latin American hospitals. The primary objective of this trial is to evaluate the effect of this multifaceted behavioral intervention on the use of two evidence-based birth practices, the selective use of episiotomies and active management of the third stage of labor (injection of 10 IU of oxytocin). Secondary objectives are to evaluate the effect of the intervention on rates of post-partum hemorrhage, use of perineal sutures and to document readiness to change among birth attendants.

Additionally, through this process we intend to improve the research capacities of a network of Latin American hospitals, and thus increase their ability to perform quality local and collaborative research studies.

## Methods/design

The study design is a two-arm cluster randomized controlled trial with hospitals as units of randomization. Hospitals will be randomized to receive a multifaceted behavioral intervention directed at developing and implementing guidelines about episiotomy use and management of the third stage of labor, or to a control group that will continue with their usual in-service training activities. Data will be collected from eligible patients at three data collection periods, one baseline period before randomization, a post-intervention period just after the end of the intervention, and a long-term follow up one year after the end of the intervention (fig 1).

**Figure 1 F1:**
[figure not shown]
Trial Profile

### Participating hospitals

Twenty four public hospitals in Argentina and Uruguay that had at least 1000 vaginal deliveries per year, and had no explicit policy for selective episiotomy or active management of third stage of labor were invited to participate. Those pre-selected hospitals that agreed to participate, collected baseline data. From the 24 hospitals, only 19 will be randomized because the analysis of their baseline data confirmed episiotomy rates in women with single vaginal births higher than 20%, and active management of the third stage of labor 25% or less.

### Randomization procedures

Since only 19 hospitals will participate in the intervention trial, random allocation may not provide adequate balance in the groups regarding important prognostic variables [21]. We will use a minimization procedure to assure balance between intervention and control hospitals on five important prognostic variables: 1) baseline episiotomy and active management rates, 2) residency programs, 3) country (Argentina-Uruguay), 4) hospital size (number of births per year), and 5) region within the country. Minimization has the advantage that it can match small numbers of similar units with respect to several unit characteristics [22], and may be considered methodologically equivalent to randomization [23].

Because all hospitals will enter the study at the same time, all prognostic variables are known in advance. A computer algorithm will be written to generate a large number of allocation sequences and to select only those sequences that minimize the imbalance between the two groups of hospitals. One of those sequences will be randomly selected by the computer and will be used to assign hospitals to the control or intervention groups. Both analysis of the baseline data and the allocation procedure will be done by an independent data center (Research Triangle Institute, North Carolina, USA) and their results communicated to the study coordinating unit. Thus, there will be a clear separation between the generator of the intervention allocation and the study coordination [24].

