### Outcome measures

The primary outcomes are aimed at changing the birth attendants' behavior relative to the rate of episiotomy and the rate of injection use of 10 I.U. of oxytocin during third stage of labor. Secondary clinical outcomes will be studied to estimate the health impact of the intervention, including the rate of perineal sutures use and the incidence of postpartum hemorrhage >500 ml. These outcomes will be assessed in singleton vaginal deliveries. We will also measure the provider's readiness to change with respect to episiotomies and management of third stage of labor with a specific questionnaire.

All outcomes will be assessed for a three-month period at three time points: at baseline (before randomization), after the end of the intervention, and the primary outcomes one year after the end of the intervention to measure the long term effects of the intervention. Interim analysis will be performed as required by the Data and Safety Monitoring Committee.

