### Data collection

Although the hospital will be the unit of analysis, we shall collect individual patient data in order to assure data quality. The goal is to accumulate data on approximately 300–500 deliveries from each hospital. All the hospitals in the project use a standard perinatal clinical record form (PIS form) [33]. This form includes the data of the obstetric history, prenatal care, labor, delivery, and neonatal outcomes. To obtain the additional necessary data to calculate the outcome variables, we will implement a modified version of the PIS clinical record that will add some variables at the bottom of the form to be addressed during the data collection periods. This approach will reduce to a minimum extra activities associated with data collection by the birth attendants during the study.

Blood loss during the third stage of labor (after delivery) will be measured from all vaginal deliveries during the data collection periods. A plastic, transparent, collection drape will be employed. At the end of the blood collection period, the amount of blood loss will be measured by pouring the contents of the drape into a calibrated pitcher. The amount of blood loss will be recorded in the data form together with the time (beginning and end) of the blood collection.

To measure provider's readiness to change, a self-administered questionnaire was designed and will be completed by all physicians and midwives at all participating hospitals, before randomization and at the end of the intervention.

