### Sample size

The sample size was estimated based upon the hospital being the unit of analysis. A preliminary analysis of data from Argentinean hospitals [2] documented a baseline frequency of episiotomies in vaginal deliveries of 42%, with a standard deviation of 11%. To protect against changes in the standard deviation [15], we have based our calculations on a standard deviation of 15%. Thus, we need 18 hospitals (9 intervention and 9 control) to identify a decrease of episiotomy rates from 40% to 20%, with a 0.05 significance level and 80% power. Considering that in public hospitals in Argentina and Uruguay about 25% of deliveries are seen among primiparae, and 75% among multiparae, a reduction of the general episiotomy rate from 40% to 20% could be achieved by reducing the rate among primiparae from 80% to 40%, and the rate among multiparae from 26% to 13%. The rates after this intervention would thus be similar to the rates achieved in a previous trial [34] and are therefore potentially attainable. Moreover, the sample size of 18 hospitals will allow identification of smaller decreases of episiotomy rates among primiparae vaginal deliveries, from 80% to 60%, with a 0.05 significance level and 80% power.

We expect the use of oxytocin during the third stage of labor to increase from 10% to 50%. However, assuming a baseline frequency of oxytocin use of 10% and a standard deviation of 5%, a sample size of 18 hospitals will provide a power > 95% to identify an increase in oxytocin use from 10% to 20%, with a 0.05 significance level. Assuming a baseline incidence rate of post-partum hemorrhage of 15% and a standard deviation of 5%, a sample size of 18 hospitals will provide a power of 84% to identify a reduction in hemorrhage from 15% to 8%.

Hospitals will initiate baseline data collection to obtain information that will be used to assess the inclusion criteria before randomization. A total of 24 hospitals were included to allow for hospital drop-outs.

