### Data analysis

Inference will be primaryly directed at the cluster (hospital) level. All analyses addressing the study research questions will use the "intention to treat" principle, comparing the outcome in the intervention group to the nonintervention group.

The outcome variables will be the percentage of primary and secondary outcomes measured during the three months following the end of the intervention. Mantel Haenszel summary risk ratios combining the individual ratios for each hospital in the intervention group and non-intervention group will be computed. The intervention and non-intervention groups will then be compared at the group level using Student's t-test on the logarithms of the summary risk ratio [17].

In addition, the data collected at the individual level will be used to explore the potential for confounding of the main effects of the intervention due to imbalances arising from the group randomization. Such multi-level analyses will use mixed model techniques (hierarchical linear models) [35,36].

For the analysis of provider's "readiness to change," the data will be summarized in terms of medians and interquartile ranges. Non-parametric statistics will be used to compare the pre- and post-intervention differences between the control and intervention groups.

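### The planned between-arm comparison of hemorrhage and perineal sutures makes inefficient use of each hospital's own baseline rate, which is collected before randomization and could serve as a covariate

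*Protocol article*

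**What the plan says.** All places are in the protocol article, Methods/design.

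- **Outcome measures.** Hemorrhage above 500 ml and perineal sutures are the two secondary clinical outcomes, meant to show health impact. On timing: "All outcomes will be assessed for a three-month period at three time points: at baseline (before randomization), after the end of the intervention".
- **Data collection.** "Blood loss during the third stage of labor (after delivery) will be measured from all vaginal deliveries during the data collection periods". Each hospital's baseline hemorrhage rate is therefore known before allocation.
- **Randomization procedures.** Because only 19 hospitals take part, allocation is constrained to balance "1) baseline episiotomy and active management rates, 2) residency programs, 3) country (Argentina-Uruguay), 4) hospital size" and region. Baseline hemorrhage and suture rates are not listed.
- **Sample size.** "a sample size of 18 hospitals will provide a power of 84% to identify a reduction in hemorrhage from 15% to 8" per cent, with an assumed SD of 5%.
- **Data analysis.** "The outcome variables will be the percentage of primary and secondary outcomes measured during the three months following the end of the intervention". Ratios for the individual hospitals are then combined by Mantel-Haenszel within each arm, and the arms are compared by Student's t-test on log risk ratios. What each hospital's ratio compares is not stated. Mixed models on individual data are added to explore confounding from imbalance, with no covariates named.

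**The concern.** With so few hospitals, the variation between them dominates the standard error. A hospital's own earlier rate is the obvious candidate to explain part of that variation, and here it is already collected. The main comparison as written either ignores it (post-intervention percentage) or fixes its weight in advance (follow-up over baseline). A fixed weight adds noise when the two periods are only weakly correlated. At stake is the precision of the trial's only bleeding outcome, and likewise of the suture comparison. The primary outcomes are not part of this point.

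**Working it through.** **Inputs from the Sample size section:** baseline 15%, target 8% (difference 7 points), between-hospital SD 5 points, significance level 0.05 (given for the preceding oxytocin calculation and taken as two-sided), 9 + 9 hospitals.

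**Input from Participating hospitals:** 19 hospitals to be randomized.

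**Assumptions:** the 19 split 9 v 10; the correlation r between a hospital's baseline and follow-up rates is not in the document, so a range is shown.

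**Step 1. The plan's own figure.** Normal formula, 9 v 9, post-only:

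- SE = 5 × √(1/9 + 1/9) = 2.357; 7 / 2.357 = 2.970
- power = Φ(2.970 − 1.960) = 0.844

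This matches the stated 84%. The noncentral t with 16 df gives 0.796 for the same inputs.

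**Step 2. Post-only, 9 v 10.** SE = 5 × √(1/9 + 1/10) = 2.297; noncentrality 7 / 2.297 = 3.047; noncentral t with 17 df gives power 0.819.

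**Step 3. Baseline rate as covariate.** Residual SD = 5 × √(1 − r²), 16 df.

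**Step 4. Change from baseline,** the additive analogue of a follow-up/baseline ratio. SD = 5 × √(2(1 − r)), 17 df.

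Power for a 7-point fall, two-sided 0.05, noncentral t, 9 v 10:

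| Assumed r | Post-only | Change score | Covariate | SD change / covariate |
|---|---|---|---|---|
| 0 | 0.819 | 0.529 | 0.816 | 7.07 / 5.00 |
| 0.3 | 0.819 | 0.680 | 0.850 | 5.92 / 4.77 |
| 0.5 | 0.819 | 0.819 | 0.910 | 5.00 / 4.33 |
| 0.7 | 0.819 | 0.959 | 0.979 | 3.87 / 3.57 |

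For a smaller fall of 5 points, post-only power is 0.537; with the covariate it is 0.573, 0.656 and 0.816 at r = 0.3, 0.5 and 0.7.

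The change score is worse than post-only below r = 0.5 and better above it. The covariate analysis is at least as good as both throughout, apart from the lost degree of freedom (0.816 v 0.819 at r = 0).

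**Scale.** These figures use absolute rates, as the Sample size section does, whereas the planned test is on log risk ratios. In a log-scale simulation with constant coefficient of variation at r = 0.3, power was about 92% for the ratio, 98% for the covariate analysis and 98% for post-only. Powers are higher and the gaps narrower on that scale, but the covariate analysis is again no worse than either alternative.

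**The case against.** - **Hemorrhage is secondary, and 19 units can balance only so much.** This stands. Reserving the allocation constraints for the baseline rates of both primary outcomes and the structural factors is defensible. Balancing on hemorrhage also does little by itself: in simulation with an unadjusted t-test it moved power for 7 points from about 82% to 84% at r = 0.5, did not improve it for 5 points (54% v 53%), and made the test conservative (type I error about 2.5%).
- **The ratios probably use baseline already.** Probably so: a hospital belongs to one arm, so a ratio for a single hospital is most naturally follow-up over its own baseline. A reader might infer from the balancing list that baseline hemorrhage is wholly unused; the Data analysis section does not support that. But a ratio is not an efficient use at low correlation.
- **Chance imbalance.** A reader might also infer that the comparison is exposed to uncontrolled bias. The baseline difference between arms of 9 and 10 under simple randomization has an SD of 2.30 points and exceeds 3.5 points with probability 0.128. However, only r times such a difference carries to follow-up (about 1 point when r = 0.3), and for a post-only comparison this variation is already in the t-test's standard error. It is not an added bias.
- **Covariates may be listed in an analysis plan not shown.** This is fair for the mixed models. But those are exploratory, and the main test is stated in the article without adjustment.

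**Conclusion.** The point holds as a forgone gain in precision, not as an error in the stated power. The 84% is correct for an unadjusted post-only comparison of 9 v 9 hospitals by the normal formula, so the documents do not support saying that power is lost against that target if the analysis is post-only. If the ratios are follow-up over baseline, the additive analogue falls below post-only whenever r is under 0.5 (68% at 0.3, on 9 v 10).

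Adjusting for the baseline rate would raise power for the planned effect from about 82% to 85%, 91% or 98% at r = 0.3, 0.5 or 0.7, with nothing gained at r = 0. The size rests on a correlation that the document does not give, across periods separated by an 18-month intervention, on the absolute-rate scale and on the 9 v 10 split. No power input is given for sutures, so the gain there is not quantified; the reasoning is the same. This is a worthwhile, low-cost improvement to two secondary comparisons.

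**What to change.** In Data analysis, make the main between-arm comparison of hemorrhage and of perineal sutures a hospital-level regression of the log post-intervention rate on arm, with the hospital's own log baseline rate as a covariate. This replaces the post-intervention percentage alone or the ratio to baseline, and removes the doubt about what each hospital's ratio compares. Cost: one residual degree of freedom (17 to 16 with 19 hospitals) and no new data.

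Optional: add baseline hemorrhage to the variables in Randomization procedures before the sequence is drawn. In a simulated allocation that took hemorrhage as unrelated to the listed factors, this cut its imbalance from 0.45 to 0.18 SD and loosened average balance on the other variables from 0.15 to 0.17 SD. It helps little without the covariate, so the analysis change should come first; it also remains possible if allocation has already taken place.
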